### Protein-enriched diet safety

Enteral complications (constipation, diarrhea, abdominal distension, and gastric residue), serum urea and total protein levels as well as any unexpected adverse event occurring during the trial will be recorded to evaluate the safety of the protein-enriched diet. The discontinuation of the enteral nutrition will be decided on the judgment of the physician looking after these patients.

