Higher protein intake has been associated with early achievement of positive nitrogen balance (NB), a surrogate of PB [19–21], promoting protein anabolism [22]. Moreover, higher protein delivery has been related to lower mortality and higher ventilator-free days in PICU patients [23, 24]. However, the exact and safe amount of protein needed to avoid negative PB remains unclear. Protein intakes greater than 3 g/kg per day have been associated with elevated serum urea nitrogen levels and metabolic acidosis [19, 20, 25, 26], but other studies have reported a higher incidence of lower intelligence quotient in very-low-birth-weight infants receiving over 6 g/kg per day of protein [27, 28].

The aim of the present study is to analyze whether the administration of a high-protein diet improves protein metabolism (serum protein levels and NB) in critically ill infants without increasing energy expenditure assessed by indirect calorimetry. A secondary objective is to register possible secondary effects of the protein-enriched diet.

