## Methods

### Hypothesis and aims of the study

The hypotheses of this study are that (1) critically ill infants receiving a higher amount of proteins on enteral feeding will experience a higher increase on serum protein levels—total proteins, albumin, prealbumin, transferrin, and retinol binding protein (RBP)—and NB than children receiving a standard enteral diet, (2) the administration of an enriched protein and high-protein-enriched diet does not increase energy expenditure in critically ill infants, and (3) protein-enriched and high-enriched protein enteral diets are well tolerated, and mild gastrointestinal side effects and tolerable serum urea and total protein elevation are adverse events.

The corresponding objectives are (1) to analyze whether the administration of a higher amount of protein on enteral diet improves protein metabolism observed by the increase of specific serum protein levels (total proteins, albumin, prealbumin, transferrin, and RBP) and NB in critically ill infants, (2) to evaluate the effect of protein supplementation on energy expenditure in these patients, and (3) to register possible secondary effects of the administration of protein-enriched and high-enriched protein diet.

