### Recruitment, randomization, and study development

Once an eligible patient is admitted to the PICU, written informed consent will be requested from parents or legal representative of the child by the physician responsible for the patient. They will be made aware that participation is voluntary, and they will be allowed to refuse further participation in the trial whenever they want.

After enrollment, the patient will be allocated randomly, in order of recruitment, into one of the three diet groups by using a randomized data table generated with EPIDAT 3.1 software (Servicio de Información sobre Saúde Pública de la Dirección Xeral de Saúde Pública de la Consellería de Sanidade, Xunta de Galicia, in collaboration with the Health Information and Analysis Unit of the Pan American Health Organization (PAHO-WHO)). A copy of the randomization list will be securely stored in an envelope located in a PICU working area desk drawer, which will be opened after patient enrollment in the study. Physicians, care givers, and investigators will know the allocation prior to the start of enteral feeding.

All patients will receive exclusively enteral nutrition via a nasogastric or transpyloric tube. The Standard Enteral Nutrition (SEN) group will be fed exclusively with cow’s milk–based infant formula (Nidina 1; Nestlé, Barcelona, Spain). The Protein-enriched Enteral Nutrition (PEN) group will be fed exclusively with a polymeric infant formula (Infatrini; Nutricia, Madrid, Spain). The High Protein-enriched Enteral Nutrition (HPEN) group will receive a polymeric infant formula (Infatrini; Nutricia) supplemented with 2.6 g of protein/100 mL of formula. The source of the protein supplement will be a non-hydrolyzed protein cow’s milk–based formula (Resource Protein Instant; Nestlé) (Table 1).

**Table 1 Tab1:** Composition of diets used in the study

	Protein (g)	Carbohydrate (g)	Lipids (g)	Energy (kcal)
Standard enteral nutrition	1.7	7.4	3.4	67
Protein-enriched enteral nutrition	2.6	10.3	5.4	100
High protein-enriched enteral nutrition	5.1	10.5	5.5	110

Content per 100 mL

Since this is an open-label trial, the assigned diet will be written down on the medical prescription of each patient and will be prepared by the PICU staff at their own unit, using for it the branded bottles where the different formulae are commercialized.

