### Study outcomes

The primary outcome of the study will be the variation of NB from baseline to the study ending and the incidence of hyperproteinemia or uremia causing the need to stop the study. Secondary outcomes include the variation of plasma protein levels (total proteins, albumin, prealbumin, transferrin, and RBP), expenditure energy measured by indirect calorimetry, and the incidence of gastrointestinal complications (abdominal distension, vomiting, diarrhea, and excessive gastric residue) and metabolic acidosis.

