### Data management

Trial data will be extracted from the medical history of the patient, registered by investigators on a data collection form, and recorded on a central database. Each patient will be identified by number of medical history and subject number, so confidentiality of the patient will be kept.

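### Outside the named items, an adverse event is recorded only if it is 'unexpected', a term left undefined in an open-label trial, so serious but anticipated events, including death, could be missed

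*Protocol article*

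**What the plan says.** The Protein-enriched diet safety section sets out what is recorded to judge safety. It starts with named items: "Enteral complications (constipation, diarrhea, abdominal distension, and gastric residue), serum urea and total protein levels". It then adds a general clause: "as well as any unexpected adverse event occurring during the trial will be recorded to evaluate the safety of the protein-enriched diet". The section does not define 'unexpected' and does not say who decides it.

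The trial is open. Under Recruitment, randomization, and study development: "Physicians, care givers, and investigators will know the allocation prior to the start of enteral feeding". Under Data management, the data are taken from the medical history, "registered by investigators on a data collection form, and recorded on a central database".

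Tolerability is one of the trial's hypotheses. Under Hypothesis and aims of the study, the third hypothesis is that "protein-enriched and high-enriched protein enteral diets are well tolerated".

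The Study outcomes section has its own list of secondary safety outcomes: "the incidence of gastrointestinal complications (abdominal distension, vomiting, diarrhea, and excessive gastric residue) and metabolic acidosis". It also makes hyperproteinemia or uremia that ends the study part of the primary outcome.

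**The concern.** A recording rule decides what can ever be analysed. If an event enters the data only when someone considers it unexpected, the safety table depends on that opinion as well as on what happened to the infants. Two features of this trial make that matter.

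First, the patients are critically ill infants, in whom many serious events can be called expected. The protocol scores their risk of mortality at admission, yet death is not named in the safety section, the study-ending section or the outcomes. Read literally, a death regarded as expected need not enter the safety data.

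Second, the people completing the forms know the diet. What they regard as expected may depend on it, so the same unlisted event could be recorded in one arm and not in another. Events never recorded cannot be recovered by any later analysis, and the trial intends to draw a conclusion about tolerability. Even if the loss were equal across arms, it would still hide serious events.

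**Working it through.** The point rests on wording, and the article states no figure for it to reproduce. The check is to list what is collected by name and see what is left to the word 'unexpected'.

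**1. Harms the article anticipates.** The third hypothesis says that "mild gastrointestinal side effects and tolerable serum urea and total protein elevation are adverse events". The Background says that protein intakes above 3 g/kg per day "have been associated with elevated serum urea nitrogen levels and metabolic acidosis". It also mentions lower intelligence quotient in very-low-birth-weight infants, which cannot be observed in a study of at most 7 days of feeding.

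**2. Where each item is collected.**

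| Item | Diet safety section | Study outcomes section | Scheduled or recorded biochemistry |
|---|---|---|---|
| Constipation | yes | no | – |
| Diarrhea | yes | yes | – |
| Abdominal distension | yes | yes | – |
| Gastric residue | yes | yes, if excessive | – |
| Vomiting | no | yes | – |
| Serum urea | yes | yes, as uremia ending the study | admission, days 1, 3, 5–7 |
| Total protein | yes | yes, as hyperproteinemia ending the study and as a level | admission, days 1, 3, 5–7 |
| Metabolic acidosis | no | yes | blood gas recorded |
| Death | no | no | – |
| Any other event | only if unexpected | no | – |

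**3. What follows.** The short-term protein harms from step 1 all appear in the table as named items, collected in every arm. The last two rows are what remains. For those, the only recording rule in the article is the 'unexpected' clause.

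The two complication lists also differ: vomiting and metabolic acidosis are missing from the safety section, and constipation is missing from the outcomes section. An investigator working from the safety section alone could take vomiting or acidosis for an expected event that need not be recorded as a safety event.

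**4. Who decides.** The article does not say. That it would be someone who knows the diet is an inference from two stated facts: staff and investigators know the allocation, and investigators complete the forms. No blinded assessor is described.

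**5. Size.** No event rates or recording rates are given, so the effect cannot be computed. The mechanism can only be illustrated with assumed values. Let the true risk of an unlisted event be 20% in the high-protein arm and 10% in the standard arm, and let a share s_H or s_S of events be left out as expected. Then

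recorded difference = 20% × (1 − s_H) − 10% × (1 − s_S).

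- s_H = 0, s_S = 0: 20 − 10 = 10 points (the true difference)
- s_H = 0.25, s_S = 0: 15 − 10 = 5 points
- s_H = 0.5, s_S = 0: 10 − 10 = 0 points
- s_H = 0.5, s_S = 0.5: 10 − 5 = 5 points
- s_H = 0, s_S = 0.5: 20 − 5 = 15 points

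So the rule can shrink, erase or inflate a difference, depending on who is under-recorded. With 30 infants per group, 10 points is 30 × 0.10 = 3 infants, and one infant is 1/30 = 3.3 points. A few unrecorded events are enough to matter.

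**The case against.** The strongest reply is that the safety sentence lists the expected events and then adds the rest, so that 'unexpected' simply means 'not on the list' and nothing falls between. That reading is possible. The words do not say it, however, and unlisted is not the same as unexpected: death in an intensive care unit is unlisted here, yet can be anticipated. If the reply states the real intention, the proposed wording only makes that intention explicit.

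A second reply is that a journal article condenses a fuller protocol, where definitions of seriousness, expectedness and death reporting would normally stand. That is fair as to missing detail, and the absence of such definitions is not the point made here. The point is a condition that the article does state. It may also be that deaths would be found in the medical history from which data are extracted, but the article does not say that they would be entered as safety data.

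A reader might infer more: that the harms anticipated from protein are themselves left out, and most of all in the high-protein arm, so that the trial is tilted towards finding the enriched diets safe. The documents do not support this. Those short-term harms are collected by name in all arms, and urea and total protein are scheduled laboratory measurements. No section says who judges expectedness. The direction is open, because background intensive-care events are expected in every arm, and unblinded staff watching for harm could over-report in the high-protein arm.

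**Conclusion.** The concern holds for events outside those named in the safety section, the outcomes section and the biochemistry schedule. For these, the article makes 'unexpected' a condition for recording, leaves it undefined, and has the forms completed by investigators who know the diet. Serious unlisted events regarded as expected, including death, could be omitted, and the omission could differ by arm in either direction.

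This rests on a literal reading of the safety sentence and on the inference that expectedness would be judged by people aware of the allocation. Neither the size nor the direction of any bias can be computed. It does not extend to the gastrointestinal effects, raised urea, raised total protein or metabolic acidosis that the article anticipates. The change is worth making because it is cheap and the lost data could not be recovered.

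**What to change.** In the Protein-enriched diet safety section, replace the reference to unexpected events with: *any adverse event, expected or not, including death*. Record each event on the same form in all three arms, with its date and seriousness. Classify expectedness afterwards, as a descriptor and not as a condition for recording. Tabulate serious events and deaths by randomized diet.

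Align the complication lists: bring vomiting and metabolic acidosis into the safety section and constipation into the outcomes section, or state why they differ.

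The cost is one change of wording and a few extra lines on the existing data collection form. The downside is somewhat more recording of background intensive-care events. No feeding or stopping rule is affected.

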### Study ending

The study will be ended:
after 7 days of enteral feeding.at PICU discharge.if hyperproteinemia greater than 8.5 g/dL is present.if serum urea levels exceed 80 mg/dL without evidence of renal function disturbance—in accordance with KDIGO (Kidney Disease Improving Global Outcomes) criteria—or suspected hypercatabolic state (underlying condition and negative nitrogen balance).

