### Statistical analysis

As there are no previous studies reporting expected standard deviations, we use the standardized difference of means for computing the optimal minimum number of patients to include in the trial. The calculation of the sample size was carried out with EPIDAT 3.1 software. Given a significance level of 5% (type I error), a power of 80% (complementary of the type II error), and a minimum detectable standardized difference of means of 0.9, we need 30 patients per group (Bonferroni correction included).

We will use an intention-to-treat approach. A descriptive analysis will be performed where quantitative variables will be described by their means and standard deviations or their medians and interquartile ranges, as appropriate. The quantitative ones will be summarized by their absolute and relative frequencies. Parametric and non-parametric tests will be employed for contrasting equality among groups.

Univariate and multivariate mixed models will be used in order to assess the effects size of the different diets (fixed effects) on the patients (random effects) unadjusted and adjusted by potential confounders, respectively. *P* values under 5% will be considered statistically significant.

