## Discussion

Current recommendations about protein prescription in critically ill children are not based on randomized controlled trial (RCT) results. Data regarding protein supplementation are lacking. Studies with small sample sizes and heterogeneous patient populations are the only source for this information. A minimum intake of protein of 1.5 g/kg per day for children admitted to the PICU [16] is the current recommendation of the ASPEN in their latest guidelines. This recommendation is supported by only a systematic review [17] and a cohort study [18].

The exact and safe amount of protein needed to avoid negative PB remains unclear. Higher protein intake has been associated with early achievement of positive NB [19–21], and higher protein delivery has been related to lower mortality and higher ventilator-free days in PICU patients [23, 24]. On the other hand, enriched protein diets have been associated with elevated serum urea nitrogen levels [19, 20, 25, 26].

This RCT is designed to obtain new data about the amount of protein needed to avoid negative PB and the amount of protein that is safe without producing secondary effects. The results of the study will be important to decide whether a protein-enriched diet will or will not be useful in critically ill infants. Moreover, the results will be clinically significant to know the exact amount of protein we can recommend for critically ill infants.

In clinical practice, there is no method that can directly evaluate the protein metabolism. On the other hand, NB and serum protein levels have been used in most previous studies to estimate an adequate protein intake. We will use NB, considering a positive NB as an indicator of protein anabolism and a negative NB as protein catabolism. Moreover, we will evaluate as an indirect indicator of a protein metabolism improvement the increase of total proteins, albumin, prealbumin, RBP, and transferrin serum levels from baseline to the study endpoint.

The main problems we will face during data collection are the possible development, in any of the groups, of side effects that recommend to stop the study and the difficulty of including enough valid patients due to problems with urine collection.

In summary, this multicenter, prospective RCT will compare the effect of three different enriched-protein diets on serum levels of proteins, nitrogen balance, and energy expenditure in critically ill infants as well as their possible secondary effects.

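### As worded, the biochemical limits end the infant's study and not only the assigned diet, so tolerance events and urea after a stop would go unrecorded

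*Protocol article*

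**What the plan says.** The Study ending section lists four events that close the study: 7 days of enteral feeding, PICU discharge, total protein above 8.5 g/dL, and a urea limit that applies "if serum urea levels exceed 80 mg/dL without evidence of renal function disturbance" and in the absence of a suspected hypercatabolic state. The first two happen to individual infants, so the list defines the end of each infant's participation.

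The section Protein-enriched diet safety states that "any unexpected adverse event occurring during the trial will be recorded to evaluate the safety of the protein-enriched diet", and that "The discontinuation of the enteral nutrition will be decided on the judgment of the physician looking after these patients".

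Under Study outcomes, the primary outcome pairs the change in nitrogen balance (NB) from baseline to the end of the study with "the incidence of hyperproteinemia or uremia causing the need to stop the study". Secondary outcomes include "the incidence of gastrointestinal complications (abdominal distension, vomiting, diarrhea, and excessive gastric residue) and metabolic acidosis".

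Statistical analysis declares: "We will use an intention-to-treat approach". Data management names the source: "Trial data will be extracted from the medical history of the patient". The Discussion gives as one purpose of the trial to learn "the amount of protein that is safe without producing secondary effects".

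**The concern.** A high urea or total protein value can be a consequence of the diet under test. If crossing a limit closes the infant's study, observation ends on an event that may depend on the assigned arm. Tolerance would then be counted over a shorter period in whichever arm stops more often, whereas an intention-to-treat comparison would normally cover the planned period in all arms.

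Two things are at stake. First, the secondary counts of gastrointestinal complications and metabolic acidosis could be too low in the arm with more stops. Second, no record is promised of what happens after a limit is crossed, including whether urea falls again. That loss does not depend on any assumed rate, and it bears on the trial's question about a safe amount of protein.

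**Working it through.** The article gives no figure on this point to reproduce: it states neither a stop rate nor a complication rate. What follows is a plausibility check and a range under stated assumptions.

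**Could stops be more frequent in HPEN?** Inputs are the composition table (Table 1) and the target of 60–65 kcal/kg per day, both in Recruitment, randomization, and study development. Protein (g/kg per day) = energy × protein per 100 mL ÷ kcal per 100 mL.

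| Arm | at 60 kcal/kg | at 65 kcal/kg |
|---|---|---|
| Standard (SEN) | 60 × 1.7/67 = 1.52 | 65 × 1.7/67 = 1.65 |
| Enriched (PEN) | 60 × 2.6/100 = 1.56 | 65 × 2.6/100 = 1.69 |
| High (HPEN) | 60 × 5.1/110 = 2.78 | 65 × 5.1/110 = 3.01 |

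HPEN therefore receives 1.83 times the protein of SEN and 1.78 times that of PEN at equal energy. The Background links intakes above 3 g/kg per day to raised urea nitrogen and acidosis. HPEN reaches that level only above 3 × 110/5.1 = 64.7 kcal/kg. More stops in HPEN are plausible but not demonstrated.

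**How much could be missed?** Assumptions, none from the documents: a 10% daily risk of a first complication on any diet, the same in infants who stop and those who do not; stops only in HPEN; 10% to 30% of HPEN infants stopped; every infant in PICU for 7 days. The sampling days 1, 3 and 5–7 come from the article.

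- True 7-day incidence with unchanged risk: 1 − 0.9^7 = 52.2%.
- Unrecorded first events per infant stopped on day d, with post-stop daily risk h: 0.9^d × (1 − (1 − h)^(7−d)).
- Loss at arm level: that value × 0.10 and × 0.30.

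| Post-stop daily risk | Stop at day 5 | Stop at day 3 | Stop at day 1 |
|---|---|---|---|
| 0 | 0 | 0 | 0 |
| 5%, per stopped infant | 0.0576 | 0.1352 | 0.2384 |
| 5%, arm level (points) | 0.6–1.7 | 1.4–4.1 | 2.4–7.2 |
| 10%, per stopped infant | 0.1122 | 0.2507 | 0.4217 |
| 10%, arm level (points) | 1.1–3.4 | 2.5–7.5 | 4.2–12.7 |

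**Effect of PICU discharge.** Discharge also ends the study, so a full 7-day window is the upper case. If infants left PICU at day 4 (an assumption), a day-3 stop with unchanged risk would lose 0.9^3 × 0.10 = 0.0729 per stopped infant, or 0.7–2.2 points at arm level instead of 2.5–7.5.

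**Yardstick.** The standard error of a difference between two arms of 30 at an incidence near 50% is √(2 × 0.25/30) = 0.129, or 12.9 points. Every value above lies below it.

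**Unobserved time.** With 3 or 9 of 30 HPEN infants stopped, the infant-days lost out of 30 × 7 = 210 are 18 or 54 for day-1 stops, 12 or 36 for day 3, 6 or 18 for day 5, and none for day 7.

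**The case against.** The strongest reply is that this is a condensed article and that follow-up after a stop may be set out in the full protocol. That is possible. But the article does fix a rule, and the rule ends the study at the limit; the point is how that rule is worded, not a missing detail.

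A second reply concerns the reading. The physician-judgment sentence is about stopping enteral nutrition altogether, so it does not settle how the assigned formula is stopped. The Study ending list may be a loose way of saying that the diet ends, and the safety sentence may refer to the trial as a whole. This stands as a caution: the literal wording supports the concern, but the intended practice may differ.

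Third, an on-diet window is a legitimate choice for judging a diet, and events after a switch may reflect the new feed. This is correct, and it is why on-diet events should still be shown separately.

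Finally, a reader might infer that intention to treat is breached, or that the primary safety count is biased. The documents support neither. No infant is moved from the assigned arm or dropped from the analysis, NB is defined up to the end of the study so a stopped infant can still contribute a value, and the stop is itself counted in the primary outcome.

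**Conclusion.** The concern holds in limited form. Followed as written, the rule ends recording on an event that may depend on the diet, and no section restores observation afterwards. This weakens the intention-to-treat comparison of tolerance.

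The size cannot be computed from the documents. Under the assumptions above, the understatement in HPEN runs from zero to a few points for most stops at day 3 to 5 (7.5 at most). Only day-1 stops with unchanged risk and a full 7-day stay bring it to 12.7 points; earlier discharge makes it smaller. It would be tempting to conclude that HPEN tolerance will be materially flattered, but that needs stop rates the article does not give, and the urea exemptions narrow the rule further. The firmer loss is descriptive: what follows a crossed limit is not recorded. This is a cheap improvement of minor priority.

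**What to change.** - **Study ending:** keep both limits and the exemptions unchanged, but let them end the assigned diet only. The infant stays in the study to day 7 after feeding began or PICU discharge, whichever is first.
- **Recording after a stop:** until then, keep extracting complications, adverse events, urea, total protein and blood gas from the medical history, and record the replacement feed and its start.
- **Reporting:** show tolerance by assigned arm over that window, with on-diet events separately.
- **Study outcomes:** state that a stopped infant's final NB value is the one at the time the assigned diet stops. Without this, moving the end of study to day 7 would leave the primary NB value undefined or post-switch in these infants. With it, the primary outcome is unchanged and no extra urine collection is needed.

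The cost is at most 6 further days of chart extraction per stopped infant, from a source already in use and with no added procedure. Two drawbacks remain: post-stop events may partly reflect the replacement feed, and routine samples may be sparser than the scheduled ones.
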